## 6.2. Selection

The effects of scanning training will be examined by comparing a group of patients receiving treatment with a group of patients on the waiting list for the treatment. During this period of ‘waiting’, the latter group functions as a control group for the patients in the training stage.

Allocation is based on the method of minimization, under the condition that allocation of the patient minimizes the difference between both groups with regard to age, sex, side of field defect, size of field defect, time since lesion and training region.

Both groups need to be sufficiently equal regarding important prognostic variables. Differences between the groups on dependent variables should be able to be described to the intervention and not to the group characteristics. Theoretically, the allocated intervention should be the only difference between the groups. Therefore, it is highly important that potentially prognostic factors such as sex, age, lesion location and time since onset do not interfere with the interpretation of the group differences. Selection bias - an unequal distribution of these prognostic factors over the groups - forms the greatest threat to internal validity. Several different randomization techniques exist, which all serve a twofold purpose: every patient should have an equal a priori chance to receive either intervention and selection bias should be ruled out. Adaptive randomization, also called minimization, is a dynamic procedure, in which chances for allocation to one of the groups are influenced by the characteristics of the patients already allocated. The procedure is based on the idea that with every allocation, the differences between the groups are minimized [10]. The Consolidated Standards of Reporting Trials (CONSORT) state that “trials that use minimisation are considered methodologically equivalent to randomised trials, even when a random element is not incorporated” [11,12]. For the sample size of our study (n = 60), it is demonstrated that adaptive randomization is not only equivalent, but even superior to unconditional randomization [13].

The moment patients are definitely included for the study, the scanning training and all effect measurements are planned based on the waiting list at Royal Dutch Visio. Allocation to one of the two groups will not affect the moment at which the training starts. At Royal Dutch Visio, a waiting list of several months preceding treatment is not unusual.

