When the waiting list is longer than 10 weeks, the patient will be allocated to either the training group or the control group based on the random allocation described above. When the waiting list is shorter, which is not expected, the patient will be allocated to the training group in case the patient belongs to this group based on the random allocation. In case the patient would belong to the control group based on the random allocation, the patient is excluded from the study, but the patient can still start scanning training within 10 weeks. Patients from both the training group and the control group will visit the University Medical Center Groningen for a pre-assessment (the week before onset of training at Royal Dutch Visio) and a post-assessment (after 10 weeks of training). The control group will participate in a third assessment, 10 weeks before the pre-assessment. (the so-called -10 assessment). By looking at the results from the pre-assessment and post-assessments of the training group and the results from the -10 assessment and pre-assessment of the control group, the effect of 10 weeks of training is compared to the effect of 10 weeks on the waiting list. In addition, the effect of treatment on the individual level can be examined by comparing the results from the post-assessment to the results from the -10 assessment and pre-assessment in the control group (within-patient repeated measures design). Including the post-assessment in the control group also increases power of the study.

The effect measurements will be performed by (student) neuropsychologists under supervision of [name]. They are not informed about the allocation to the training group or the control group and therefore they do not know whether the patient already received training or not.

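### The 10-week waiting-list threshold in Protocol 6.2 is up to one week, plus booking time, shorter than the control group's own visit schedule requires

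*Protocol*

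**What the plan says.** Section 6.2 sets the entry rule: "When the waiting list is longer than 10 weeks, the patient will be allocated to either the training group or the control group". A patient with a shorter wait stays in the study if allocated to training and is excluded if allocated to control.

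The visits are then fixed as follows (section 3 gives the same schedule):

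- Before training, every patient is seen once, whichever the group: "pre-assessment (the week before onset of training at Royal Dutch Visio").
- Once training is done, every patient is seen again: "post-assessment (after 10 weeks of training").
- Controls alone have one more visit, earlier than these two: "The control group will participate in a third assessment, 10 weeks before the pre-assessment".
- The intended contrast is that "the effect of 10 weeks of training is compared to the effect of 10 weeks on the waiting list".

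Two further statements in 6.2 limit the room for adjustment. The training date does not respond to allocation: "Allocation to one of the two groups will not affect the moment at which the training starts". Visits are not booked in advance of inclusion: "The moment patients are definitely included for the study, the scanning training and all effect measurements are planned based on the waiting list".

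The protocol also says that waits of several months are not unusual and that waits below 10 weeks are not expected.

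**The concern.** The threshold and the control schedule use different reference points. The threshold runs to the start of training. The control's 10 weeks run back from the pre-assessment, which comes before that start. The gap between the two, and the time needed to arrange a visit to Groningen, are not in the threshold.

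A patient whose wait is only just over 10 weeks passes the rule and may be allocated to control, with little or no slack to fit the -10 visit. If it does not fit, the site can shorten the waiting interval, move the training date or lose the control, and the protocol does not say which. A training-group patient with the same wait needs only the pre-assessment and has no such difficulty. Any loss or rescheduling would therefore fall on one arm, in a trial whose section 6.2 names selection bias as the greatest threat to internal validity.

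A second, smaller question is whether the two intervals being compared are the same length.

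**Working it through.** **Inputs** (section 6.2; training start is day 0; 10 weeks is read as 70 days)

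- Wait from allocation to training start: W > 70 days. That the wait is counted from allocation to training start is my reading; the rule for short waits, which speaks of training starting within 10 weeks, supports the end point.
- Gap from pre-assessment to training start: g = 1 to 7 days.
- -10 assessment to pre-assessment: 70 days.
- Post-assessment: 70 days after training start at the earliest; no latest date is given.
- Booking time from allocation to the -10 visit: L, not given in the protocol.

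**Step 1. The plan's own figure.** The wait a control needs is

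W_min = 70 + g + L.

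The stated 70 days comes back only with g = 0 and L = 0, that is, with the pre-assessment on the day training starts and the -10 visit on the day of allocation. The first of these is outside the stated week.

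**Step 2. What the schedule needs, with L = 0, and the two intervals**

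| Pre-assessment, days before training (g) | Wait needed, days (70 + g) | Weeks | -10 to pre, days | Pre to post, days (70 + g) | Excess (g/70) |
|---|---|---|---|---|---|
| 1 | 71 | 10.14 | 70 | 71 | 1.4% |
| 3 | 73 | 10.43 | 70 | 73 | 4.3% |
| 5 | 75 | 10.71 | 70 | 75 | 7.1% |
| 7 | 77 | 11.0 | 70 | 77 | 10.0% |

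The pre-to-post figures assume that the post-assessment follows at once after 10 weeks of training. A later visit lengthens that interval further.

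**Step 3. Slack for a patient just over the threshold.** The most booking time available, with the pre-assessment held on the last possible day (g = 1), is W - 71:

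| Wait W, days | Days of the pre-assessment week that are usable | Most days to arrange the -10 visit |
|---|---|---|
| 71 | 1 | 0 |
| 74 | 4 | 3 |
| 77 | 7 | 6 |

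The two columns trade off: using an earlier pre-assessment day takes away booking time one for one. At 71 days the only workable plan is a -10 visit on the day of allocation and a pre-assessment on the day before training.

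**Step 4. Threshold that leaves the whole pre-assessment week open.** 70 + 7 + L = 77 + L days. With an assumed L of 0 to 14 days this is 77 to 91 days, or 11 to 13 weeks.

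**Step 5. Number affected.** This needs the distribution of waits and L. The protocol gives neither, so no number follows.

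**The case against.** The strongest reply is that the schedule is tight but not impossible. The rule says longer than 10 weeks, the pre-assessment may fall on any day of its week, and a 71-day wait does fit on paper. Section 6.2 also has training and all measurements planned together once the patient is included, so the training date is known when visits are booked. That stands: a reader might infer that controls near the threshold cannot follow the plan, and the protocol does not support that. They can, but only with an immediate -10 visit and a late pre-assessment.

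A reader might also put a figure on the loss. Assuming waits spread evenly over 10 to 26 weeks and 1 to 2 weeks to book, with the full one-week gap, 2/16 to 3/16 (12.5% to 19%) of controls would be affected, or about 4 to 6 of 30. Neither assumption has a basis in the protocol, which expects waits of several months. The base is also doubtful, because 30 per group is the number left after losses (section 4.4: 75 remaining before the training period, 60 after). With prompt booking and a late pre-assessment the share approaches zero.

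On unequal intervals, the reply is that the sentence compares 10 weeks of training with 10 weeks of waiting as exposure, and the extra days are untrained. Patients are at least six months from onset with a stable condition (section 4.2), so a difference of up to a week is unlikely to move the eye-movement outcomes much. That also stands.

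Finally, the statement that allocation leaves the training date unchanged is a design statement. The text at hand does not show that it was given to patients as a promise.

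What the reply does not remove is that the threshold omits a gap which the same section creates, and that only controls bear the consequence.

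**Conclusion.** The threshold does not fit the schedule in its own section. It falls short of the wait a control needs by up to one week (77 against 70 days), plus booking time. Near the threshold the plan works only under favourable timing. Otherwise it forces a shortened interval, a delayed training start that contradicts the protocol, or a lost control, and in the control arm only.

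The number of patients affected cannot be computed and may be small. The 1 to 7 day difference between the intervals is real on a literal count. It also enters the within-control comparison in section 8.2, if T1 to T3 there are the -10, pre- and post-assessments. It probably has little effect on bias.

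The written exclusion of short-wait patients from the control arm after allocation is a separate weakness. The one-sided loss described here is a consequence inferred from the timing, not a rule in the plan. The sample size calculation is not affected.

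This is a minor point, worth correcting because the correction is cheap. It rests on reading the wait as running from allocation to training start and 10 weeks as 70 days.

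**What to change.** Reconcile the threshold, the visit timing and the statement on training start in sections 3 and 6.2:

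1. State the threshold from the schedule. The planned time from allocation to training start must cover the pre-assessment week, the full control interval before it and the booking time the sponsor needs: at least 11 weeks plus that booking time.
2. Check it for every patient before allocation, and do not allocate those who fall short. This replaces the rule that excludes short-wait patients after allocation in the control arm only.
3. Give the -10-to-pre and pre-to-post intervals the same nominal length and the same visit window in both arms. If this is done by lengthening the control interval, the threshold moves with it: at the maximum of 77 days it becomes 77 + 7 = 84 days (12 weeks) plus booking time.

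The cost is a few sentences and one planning check per patient. A few patients with waits just over 10 weeks would not be randomised, and short-wait patients who would have entered the training group would no longer do so. Since the protocol expects waits of several months, the loss should be small, but the sponsor should confirm this against its own waiting-list data.

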## 4.2. Inclusion criteria

- Homonymous visual field defects (quadrantanopia at minimum, three quarters affected at maximum, based on binocular Goldmann perimetry, isopters: V-4e, III-4e, I-4e, I-2e and I-1e, monocular Goldmann III-4e, and monocular Humphrey monocular 10-2), due to acquired post-chiasmatic brain injury.
- At least six months between onset of HVFD and first effect measurement
- Neurological condition is stable
- Ophthalmological condition stable for at least six months
- Age between 18 and 75 years
- Self-reported mobility-related difficulties
- Able to walk at least 50 meters independently or by using a cane/rollator, without a wheelchair (mobility assessment has to be possible, training is aimed at mobility in and around the house).
- Best corrected binocular visual acuity 0.5 (Lighthouse ETDRS 2000 chart, 4m, 500 lux, using optimal correction).
- Peak log contrast sensitivity within normal limits (Vistech VCTS6500, 4m, 500 lux, >B5 or C4)
- Eye and head mobility undisturbed in all directions
- MMSE score >25
- Sufficient memory for remembering training instructions and homework assessments (based on 8WT)

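### Patients with a waiting list under 10 weeks stay in the trial if allocated to training and are excluded if allocated to control, so any such patients can appear in one arm only

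*Protocol*

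**What the plan says.** Protocol section 6.2 (Selection) sets two rules according to the length of the waiting list.

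- Long wait: "When the waiting list is longer than 10 weeks, the patient will be allocated to either the training group or the control group", according to the minimisation procedure.
- Short wait: "When the waiting list is shorter, which is not expected, the patient will be allocated to the training group in case the patient belongs" there by the random allocation. For the other arm the rule is "In case the patient would belong to the control group based on the random allocation, the patient is excluded from the study"; such a patient may still begin training within the 10 weeks, but outside the study.

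The same section describes when this happens: "The moment patients are definitely included for the study, the scanning training and all effect measurements are planned based on the waiting list". It also says "Allocation to one of the two groups will not affect the moment at which the training starts". On how often short waits will arise, it offers only that they are not expected and "At Royal Dutch Visio, a waiting list of several months preceding treatment is not unusual"; it gives no figure.

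Waiting time is not among the inclusion or exclusion criteria (sections 4.2 and 4.3). Nor is it a minimisation factor; those are listed as balancing the groups "with regard to age, sex, side of field defect, size of field defect, time since lesion and training region".

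**The concern.** The exclusion depends on the arm and acts once the allocation is known, on patients who have already met the entry criteria. Among short-wait patients, those allocated to training are retained and those allocated to control are removed. A retained short-wait patient could not have been a retained control. Section 6.2 sets its own standard for allocation: the same prior probability of either group for everyone, and no selection bias. The short-wait rule fails that standard for these patients. Balancing on region or time since lesion does not balance waiting time itself.

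What is at stake is the first analysis in section 8.2, the between-group comparison at T2, which is only possibly corrected for T1. If short-wait patients differ in outcome from long-wait patients, part of that difference enters the estimated training effect.

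**Working it through.** **Inputs from the Protocol.** Section 4.4 gives an effect size of 0.65 SD, two independent groups, one-sided α = 0.05, power 0.80, 30 per group, and 75 patients remaining after the entry criteria are checked.

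**Inputs that are assumptions.** These are the share s of allocated patients with a short wait, and the outcome difference d (in SD) between short-wait and long-wait patients. The Protocol gives neither.

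**The plan's own figure.** By the normal approximation, n per group = 2 × (1.645 + 0.842)² / 0.65² = 29.3, rounded up to 30. With the t distribution n is 29.97, and power at 30 per group is 0.800. The stated 30 per group is reproduced.

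**Effect of the rule.** With 1:1 allocation, a share s of the training arm has a short wait, against none of the control arm. With no true training effect, the expected group difference is

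bias = s × d.

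The standard error of the difference in SD units is √(2/30) = 0.2582. The one-sided type I error is then

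1 − Φ(1.645 − s × d / 0.2582).

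With d = 0.5 SD in favour of training:

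| Share s | Controls excluded, 75 × s/2 | Bias (SD) | Bias / 0.2582 | 1.645 minus that | Type I error |
|---|---|---|---|---|---|
| 2% | 0.75 | 0.010 | 0.039 | 1.606 | 5.4% |
| 5% | 1.9 | 0.025 | 0.097 | 1.548 | 6.1% |
| 10% | 3.8 | 0.050 | 0.194 | 1.451 | 7.3% |
| 20% | 7.5 | 0.100 | 0.387 | 1.258 | 10.4% |

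Over the same shares, type I error runs from 5.2% to 6.8% with d = 0.2 SD and from 5.7% to 15.3% with d = 0.8 SD.

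**Opposite direction.** If short-wait patients do worse, the sign reverses. At s = 10% and d = 0.5 SD the error is 1 − Φ(1.645 + 0.194) = 1 − Φ(1.839), about 3.3%, and the bias works against training.

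**Power.** If the excluded controls are not rebalanced, 60 retained patients would split about 33 to 27 at a 20% share. Power by the normal approximation is then 0.804, against 0.809 with equal groups. The issue is therefore bias and not sample size.

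**Length of wait needed.** The pre-assessment is in the week before training, and the -10 assessment is 10 weeks before the pre-assessment (sections 3 and 6.2). A control patient therefore needs 10 weeks plus the assessment week, about 11 weeks, between allocation and the start of training. A threshold of 10 weeks alone falls slightly short of this.

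**The case against.** The strongest reply is that the rule is a contingency for something the Protocol does not expect. If no short waits occur, it never acts. At shares of 2% to 5% and d = 0.5 SD, type I error stays close to nominal. Bias also requires that waiting time be related to outcome, which the Protocol neither shows nor rules out. A T1 correction would shrink any part that comes from baseline differences. The second analysis in section 8.2, within the control group, has no between-arm comparison to distort. All of this stands and limits the severity. It does not justify keeping an exclusion that depends on the arm.

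Three stronger readings are tempting, and the Protocol does not support them.

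- **That the comparison could not be repaired.** Training start is stated not to depend on the allocated group, so waiting time is a baseline variable. Restricting the training arm to patients with a long enough wait would remove the imbalance this rule creates.
- **That section 6.2 itself names this rule as its main threat to validity.** That remark concerns unequal distribution of prognostic factors such as sex, age, lesion location and time since onset. Waiting time is not listed, and nothing in the Protocol links it to region or referral route.
- **That the six-month criterion has the same fault.** It reads "At least six months between onset of HVFD and first effect measurement", and the first measurement comes 10 weeks earlier in the control group. A reader might infer that some recent-onset patients qualify only for training. But section 3 decides inclusion (step 4) before allocation (step 5), and nowhere are controls dropped under this criterion. Section 4.1 simply requires a defect of at least 6 months. Even on that reading, both arms have the same minimum time since onset at the start of the interval compared: pre to post for training, -10 to pre for control. Moving everyone to one common date would make that minimum 10 weeks later in the training arm, which is a trade-off and not a clear correction.

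**Conclusion.** The rule is wrong as written and should be fixed. It removes patients according to the arm they were allocated to, against the Protocol's own standard for allocation. That follows from the text alone.

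The size of the harm cannot be determined from the Protocol. It is zero if no short waits occur or if waiting time is unrelated to outcome. Under the assumed 0.5 SD difference favouring training, the bias is 0.01 to 0.10 SD for shares of 2% to 20%, and one-sided type I error is about 5.4% to 10%, before any T1 correction. The upper end of that range sits uneasily with the statement that short waits are not expected, and the direction could be the reverse. The text does not support saying that the arms are in fact non-comparable, only that the rule permits it.

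**What to change.** 1. Establish the planned training start before allocation. Section 6.2 already plans training and measurements at definite inclusion, so the date should be available.
2. Allocate only patients whose wait has room for both the -10 assessment and the pre-assessment, that is, 10 weeks plus the assessment week. Apply this identically whichever arm would follow. Patients with a shorter wait are not allocated to either arm and follow usual care.
3. Delete the provision that excludes only control-allocated patients.
4. If short-wait patients have already entered the training arm, restrict the between-group analysis to patients whose wait was long enough for either arm.

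The cost is a short amendment and the loss of the short-wait patients who would have joined the training arm, few by the Protocol's own expectation. The required size stays at 30 per group, and with no short-wait patients in either arm the bias from this rule is zero. No change to the six-month criterion is proposed.

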5. In case the patient is included and has given informed consent, the patient is randomly allocated to the training group or control group (method of minimization, see for more information section *6.2 Selection*). Allocation to one of the two groups will not affect the moment at which the training starts. At Royal Dutch Visio, a waiting list of several months preceding treatment is not unusual. Patients from both the training group and the control group will visit the University Medical Center Groningen for a pre-assessment (the week before onset of training at Royal Dutch Visio) and a post-assessment (after 10 weeks of training). The control group will participate in a third assessment, 10 weeks before the pre-assessment (the so-called -10 assessment). By looking at the results from the pre-assessment and post-assessments of the training group and the results from the -10 assessment and pre-assessment of the control group, the effect of 10 weeks of training is compared to the effect of 10 weeks on the waiting list. In addition, the effect of treatment on the individual level can be examined by comparing the results from the post-assessment to the results from the -10 assessment and pre-assessment in the control group (within-patient repeated measures design). Including the post-assessment in the control group also increases power of the study.

In order to provide compensatory scanning training close to the patients’ residence, training will be provided at several locations of Royal Dutch Visio throughout the Netherlands, including Haren, Leeuwarden, Apeldoorn, Rotterdam and Haarlem. The final training protocol is composed in Haren. Therapists working at the participating departments of Visio received additional education in providing the training conform protocol. The training and diagnostic assessments take place at the department of Visio where the patient has registered.

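### Section 6.2 applies the 10-week waiting-time condition after allocation and to the control arm only, so short-wait patients can appear only in the training arm

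*Protocol*

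**What the plan says.** Section 3 (Design) sets the order of steps: "In case the patient is included and has given informed consent, the patient is randomly allocated to the training group or control group". Allocation therefore follows inclusion and consent.

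Section 6.2 (Selection) then makes three provisions that depend on the waiting list:

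- Long wait: "When the waiting list is longer than 10 weeks, the patient will be allocated to either the training group or the control group".
- Short wait, training drawn: "the patient will be allocated to the training group in case the patient belongs to this group based on the random allocation".
- Short wait, control drawn: "In case the patient would belong to the control group based on the random allocation, the patient is excluded from the study". The patient may then start training outside the study.

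The short-wait case is introduced with "When the waiting list is shorter, which is not expected", and the section remarks that "a waiting list of several months preceding treatment is not unusual". No distribution of waiting times is given.

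Section 6.2 also states what any randomisation technique should achieve: "every patient should have an equal a priori chance to receive either intervention and selection bias should be ruled out". Allocation is by minimisation on six factors: training region, time since lesion, age, sex, and the side and size of the field defect. Waiting time is not one of them.

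**The concern.** The exclusion acts after inclusion, depends on the allocation result and operates in one arm only. The control arm is drawn from long-wait patients; the training arm is drawn from patients with any wait. If short-wait patients differ in outcome, that difference enters the between-group comparison, which is the first analysis listed for the primary outcome in Section 8.2. Having a control schedule that needs 10 weeks of waiting is a sound reason to require a sufficient wait. It is not a reason to require it of one arm only.

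**Working it through.** **Step 1. What the rule implies.** Among short-wait patients who remain in the study, P(training) = 1 and P(control) = 0. This follows from the text without any assumption. Set beside the section's own aim of an equal chance and no selection bias, the two do not agree. Minimisation chooses between arms, but a short-wait patient sent to control leaves the study, so no choice of factors can produce a short-wait control.

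**Step 2. The plan's own sample size.** Inputs from Section 4.4: effect size 0.65, one-sided α = 0.05, power 0.80, two independent groups.

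n per group = 2(1.645 + 0.842)² / 0.65² = 29.3, rounded up to 30. The t-test version gives 29.97, also 30. The stated figure reproduces and is not in dispute. Power at 30 per group is 0.81 by the normal approximation and 0.80 by the t-test.

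**Step 3. Bias.** Two inputs are not in the protocol and are assumed: s, the share of short-wait patients among those allocated, and δ, their outcome difference from long-wait patients in SD units. Training keeps everyone, so its short-wait share is s; in control it is 0. With no training effect, the expected difference between arms is s × δ − 0 × δ = s × δ.

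For an unadjusted comparison with 30 per arm, the standard error is √(2/30) = 0.258 SD. The one-sided false-positive rate is 1 − Φ(1.645 − sδ/0.258) if the bias favours training, and 1 − Φ(1.645 + sδ/0.258) if it favours control. With δ = 0.5:

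| s | Bias (SD) | Rate, bias favours training | Rate, bias favours control |
|---|---|---|---|
| 0 | 0 | 0.050 | 0.050 |
| 0.05 | 0.025 | 0.061 | 0.041 |
| 0.1 | 0.05 | 0.073 | 0.033 |
| 0.2 | 0.10 | 0.104 | 0.021 |
| 0.3 | 0.15 | 0.144 | 0.013 |

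The noncentral t gives 0.103 and 0.142 in place of 0.104 and 0.144. With δ = 0.25 the biases halve, and the rates favouring training are 0.055, 0.061, 0.073 and 0.088 for s = 0.05, 0.1, 0.2 and 0.3.

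**Step 4. Effect of using baseline.** Let δ1 and δ2 be the short-wait difference at T1 and T2. The bias in change scores is s(δ2 − δ1); with T1 as a covariate of slope b it is s(δ2 − bδ1). A stable level difference (δ1 = δ2 = δ) gives 0 and sδ(1 − b) respectively. The full s × δ remains only if the whole difference arises during the 10 weeks, that is, if a short wait predicts the change itself. Sections 3 and 6.2 describe comparing changes; Section 8.2 makes correction for T1 optional.

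**Step 5. Power.** If 60 are allocated 30:30 and excluded controls are not refilled, s = 0.1, 0.2 and 0.3 leave 27, 24 and 21 controls, with t-test power of 0.78, 0.76 and 0.73 against 0.80. If the analysed total is held at 60, the training share is 1/(2 − s). The arms are then about 31.6:28.4, 33.3:26.7 and 35.3:24.7, with power 0.81, 0.80 and 0.80 against 0.81 (normal approximation).

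**The case against.** The strongest reply is that this is a contingency rule for a case the protocol does not expect. At s = 0 it does nothing, and both s and δ above are assumptions. That stands as a limit on the size of the harm. It does not rescue the rule, which matters only when the case occurs and then gives the wrong answer. A statement about what is not unusual is also not a minimum wait, and training is offered at several locations.

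Several stronger readings are tempting but not supported:

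- **A materially biased primary comparison.** No figure in the protocol shows this. The direction is unknown, and a level difference cancels or shrinks once baseline is used. Region and time since lesion are minimised, which limits imbalance through those two routes. The entry criteria (at least six months since onset, stable condition) make urgency a weak route.
- **A training-arm short-wait share always equal to s.** Section 6.2 does not say whether excluded controls stay in the minimisation tally. In a simulation with minimisation on region and total, 60 analysed patients and one of five regions short-wait (s = 0.2), the share was about 20% if they are counted. If they are not, it was about 5.5% with deterministic allocation or 12% with a 0.8 biased coin. If short waits are unrelated to region, the share stays near s either way.
- **A lever for removing unwanted controls by shortening their wait.** Sections 3 and 6.2 both say that allocation does not alter when training starts, and "The moment patients are definitely included for the study, the scanning training and all effect measurements are planned based on the waiting list". Such a manoeuvre would breach the protocol.
- **A definite loss of power, or an error in the recruitment funnel.** The loss arises only if excluded controls are not refilled. Section 6.5 replaces withdrawals and does not mention these patients. The absence of a funnel line in Section 4.4 is consistent with none being expected.

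It can also be said that the equal-chance sentence describes randomisation techniques in general. It does, but the section gives it as the justification for the chosen method, so the short-wait rule should be held to it.

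**Conclusion.** The rule is wrong as written and should be fixed. That short-wait patients can be analysed only in the training arm is certain from the text; the consequence is conditional. It is nil if no short waits occur. Otherwise the bias is at most about s × δ in either direction: 0.05 SD at s = 0.1 and δ = 0.5, which is 0.05/0.65 = 8% of the planning effect size. These values are illustrative. They rest on an assumed s and δ, a short-wait share of s in the training arm, and an unadjusted comparison of 30 per arm. Nothing in the protocol shows that the trial's conclusion would be compromised.

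**What to change.** In Section 4.2, add as an eligibility criterion that the planned training start leaves enough time to complete the control schedule. Check it for every patient against the Visio planning date, before allocation. This is feasible because Section 6.2 plans training at definite inclusion, and Section 3 places inclusion before allocation. In Section 6.2, delete the arm-dependent rule and state that everyone allocated is analysed in the allocated arm, even if the wait later changes. Short-wait patients then enter neither arm and can start training outside the study, which the protocol already allows for those it excludes.

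The cost is a wording amendment to two sections and the loss of the short-wait patients who would have entered the training arm, who should be few on the protocol's own expectation. The short-wait share becomes zero in both arms, the bias from this rule is removed, and the planned 30 per group stays the same.
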